#### Qualitative analysis

Interviews will be conducted by a researcher who will not be involved in the delivery of the intervention. Interviews will be digitally audio-recorded, anonymised and transcribed verbatim by a professional transcriber. Original audio files and file transcripts will be stored on a secure server at King’s College London (KCL) in a password protected file. The transcriber will delete his/her copy of each audio file once transcription is complete. Data will be analysed using thematic analysis [108] and, if appropriate, NVivo11 software for data management. Analysis begins with a coding framework, where key concepts emerging from the transcripts will be mapped. Additional themes emerging are added to the coding framework. The final framework is agreed, then applied to all transcripts. An iterative process will confirm a final coding framework before analysis. Two researchers will code all transcripts independently and then compare and refine resulting codes and themes in discussion. The emergent themes will form the basis of analytical interpretation. Process evaluation data will be analysed separately from outcome data in order to avoid bias in interpretation [109].

### Study outcome measures

For feasibility and acceptability outcomes, please refer to Study outcome measures. The primary and secondary outcome measures will be recorded at baseline, three, six and 12 months post randomisation. The primary outcome measure will be utilised to assess initial estimates efficacy of the intervention in the CBT intervention group compared to the Fatigue Information Sheet group. All outcome measures have been validated for self-completion.

### Primary outcome measure

#### IBD-Fatigue Scale (IBD-F)

The IBD-F [110] aims to assess IBD-specific fatigue. The first two sections of the questionnaire, five questions assessing frequency and severity of fatigue and 30 questions rating the experience and impact of fatigue, will be utilised in the study. Higher scores indicate higher fatigue and higher impact of fatigue. Initial validation of the measure suggested that the questionnaire had good face and content validity, acceptable to excellent test–retest stability and a high degree of internal consistency [110]. Both sections of the IBD-F have been found to be significantly correlated with other widely utilised fatigue scales [22]. The scale was developed by conducting in-depth interviews with participants with IBD, in order to gain insight into their experience and ultimately to represent issues of specific importance to people with IBD fatigue.

### Explanatory variables

#### Disease activity indexes

The Harvey Bradshaw Index (HBI) [114] and the Simple Clinical Colitis Activity Index (SCCAI) [115] will be utilised to measure disease activity for CD and UC patients, respectively. The HBI and SCCAI will be recorded at baseline, three, six and 12 months post randomisation. All other explanatory variables will only be recorded at baseline and three months post randomisation.

#### Brief Illness Perceptions Questionnaire (BIPQ)

The BIPQ [116] uses a single-item scale approach to assess illness perceptions. It is a shorter version of the original Illness Perception Questionnaire (IPQ) [117] which is utilised to assess five dimensions within a cognitive representation of illness. The brief version consists of nine items: five of the items assess cognitive illness representations (consequences, timeline, personal control, treatment control and identity), two of them assess emotional representation (concern and emotions) and one item assesses illness comprehensibly. Each item (e.g. ‘How concerned are you about your fatigue?’) is rated using a response scale of 0–10; in which higher scores represent more threatening views of fatigue. The psychometric properties of this measure have been assessed using samples from several illness groups including IBD [118] and chronic obstructive pulmonary disease [119].

#### Epworth Sleepiness Scales (ESS)

The ESS [120] is utilised to measure a participant’s level of daytime sleepiness. From a clinical point of view this is relevant in that it helps to determine the presence of pathology or simply predict whether sleep onset is likely to occur at inappropriate times [121]. The questionnaire asks participants to rate their chance of falling asleep or dozing on a scale of 0–3 in eight soporific situations, ranging from ‘Lying down to rest in the afternoon when circumstances permit’ to ‘in a car while stopped for a few minutes in traffic’. A total score of 0–24 is determined, with values over 10–11 indicating abnormal or pathological sleepiness. Given its ease of use and cost-effectiveness, the ESS in now one of the most widely used tools for the assessment of sleepiness [122].

#### Seven-item Generalised Anxiety Disorder Scale (GAD7)

The GAD7 [123] asks participants how often during the last two weeks they have been bothered by each of the seven core symptoms of generalised anxiety disorder. Response options are ‘not at all’, ‘several days’, ‘more than half the days’ and ‘nearly every day’, scored as 0, 1, 2 and 3, respectively. It has a minimum possible score of 0 and a maximum possible score of 21. The GAD7 has been utilised in studies assessing anxiety severity in diverse conditions, including: patients with eating disorders [124]; multiple sclerosis [125]; and cardiovascular disease [126]. The GAD7 is used as an outcome measure for CBT for anxiety in the UK Improving Access to Psychological Therapies (IAPT) programme [127].

#### Nine-item Patient Health Questionnaire (PHQ9)

The PHQ9 [128] is based on the diagnostic criteria for major depressive disorders in the Diagnostic and Statistical Manual, Fourth Edition (DSM-IV). The questionnaire contains nine items, which are scored from 0 (not at all) to 3 (nearly every day), according to the frequency of their experience over the previous two-week period, with a total score in the range of 0–27. The PHQ9 has been found to be a reliable and valid measure [129] and it has been previously validated in gastroenterological patients [130]. The PHQ9 is used as an outcome measure for CBT for depression in the IAPT programme.

### Sociodemographic and clinical data

Sociodemographic and clinical data about participants will be collected at baseline in order to better characterise the sample, make the results of the RCT more clinically relevant and appropriately adjusting statistical data analysis. Sociodemographic data collected will include: age; gender; marital status; education status; employment status; and living arrangements. Clinical data will include: IBD diagnosis; co-morbidities; latest measurement of faecal calprotectin concentration; IBD-related medications (name, dose and frequency); length of time since diagnosis (years, months); number of IBD-related surgeries; smoking status (current smoker, ex-smoker, never smoked); exercise status (> or < 30 min of aerobic exercise per week); haemoglobin; ferritin; serum albumin; C-reactive protein (CRP); platelets count; vitamin B12; and folate. These clinical data are routinely collected as part of standard care in patients with IBD at these sites. If the patient does not attend the service at follow-up, it is unknown whether there will be updated clinical data for patients. However, due to potential patient burden and lack of funding, no additional blood tests will be conducted for the patients, even if recent clinical data are not present in the hospital patient records. One value for each clinical marker will be collected if it refers to up to three months prior to or after the completion of the baseline questionnaires.

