Eligible patients will then be given at least 48 h to consider their participation in the study and discuss the decision with family, friends and their care team. A member of the research team will then contact them by telephone to answer any additional questions, verify their understanding of what is involved and confirm their interest in study participation. If patients agree to take part in the study, they will be asked to sign the *Patient Consent Forms-RCT* and complete the *Baseline Data A* booklet. A format for written questions for this phase has been developed and piloted with our PPI group to ensure acceptability and ease of understanding of questions to be asked. Participants will be asked to return the signed *Patient Consent Forms-RCT* and the completed questionnaires in the pre-paid stamped addressed envelope provided within seven days of receipt. The returned study documents will be checked for completeness, and the patient will then be entered into the randomisation database for the RCT and told whether they are in Group 1 (CBT manual + therapist support) or Group 2 (Fatigue Information Sheet only). Screening and consenting will continue until the study target sample size (*n* = 40, 20 for each arm) is reached. Hospital consultants will be informed of the patients’ participation in the study via an entry made in the patient’s notes; with patients’ agreement, their General Practitioner (GP) will be informed using *GP Notification Letter*.

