#### Randomisation

Consenting participants will be randomised to CBT manual plus therapist support or Fatigue Information Sheet only using a random number generator with a 1:1 ratio in the Statistical Package for the Social Sciences Version 22. All baseline information will be collected prior to randomisation. Participants will be randomised at the individual level. The randomisation sequence will be generated electronically by an independent statistician prior to the commencement of the study. The statistician will have no patient contact. The trial coordinator (blinded until this point) will access the randomisation database to assign patients to the two groups. Indeed, as this is a small pilot study on a limited budget, there are no resources available to provide a blinded data collector. Owning to the nature of the study the participants, the researchers and the therapist will not be blinded to treatment allocation after randomisation. The trial coordinator will be informed of the outcome of the randomisation procedure in order to identify participants who require telephone support calls during the trial. The researcher conducting the qualitative interviews will also be unblinded to ensure that appropriate questions are asked.

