#### Group 1 (CBT manual + therapist support)

Group 1 participants will receive a CBT manual for the management of fatigue and have one 60-min session and seven 30-min telephone/Skype sessions with a therapist over an eight-week period. All sessions will be over the telephone or Skype according to patient preference. In the Consent Form, patients will be informed that if they choose Skype, information may not be secure and may be transferred to other countries outside the Trust’s control. During the intervention, participants will have access to all usual care, including the nurse-led helpline.

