Primary and secondary measures at baseline along with recruitment rates, telephone session attendance, time spent on the intervention, Homework Sheet completion rates and withdrawal from intervention rates will be presented as means and standard deviations for approximately normally distributed continuous variables, medians and interquartile ranges for non-normally distributed variables, frequencies and percentages for categorical variables. Initial estimates of treatment effect on primary and secondary outcomes at the follow-up assessments will use an intention-to-treat (ITT) framework, implemented using a regression model, adjusting for baseline values of the outcome, sociodemographic and clinical outcomes. ITT analysis will compare the primary and secondary outcome measures at three months between the two randomised groups. ITT analysis will compare only primary outcome measures at six and 12 months between the two randomised groups. Where participants wish to withdraw from the intervention, we will attempt to retain them in the data collection, unless they express a wish to be withdrawn completely.

As this is a pilot study, it is not intended that the study is powered to detect significant differences on the primary or secondary outcome measures. Qualitative data will also be recorded. Protocol conforms to Standard Protocol Items: Recommendations for Interventional Trials (SPIRIT). See Additional files 1 and 2 at the end of the manuscript for SPIRIT Figure and Checklist.

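### Clinical markers counted as baseline may be dated up to three months after the baseline questionnaires, so post-randomisation values could enter the baseline table and the adjusted comparison

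*Protocol article*

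**What the plan says.** All of this is in the Protocol article.

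- **Sociodemographic and clinical data.** These data are described as collected at baseline, and one stated purpose is "appropriately adjusting statistical data analysis". The list includes faecal calprotectin, haemoglobin, ferritin, albumin, CRP, platelets, vitamin B12 and folate. No study blood tests are done, so each value comes from routine care. One value per marker "will be collected if it refers to up to three months prior to or after the completion of the baseline questionnaires".
- **Randomisation.** "All baseline information will be collected prior to randomisation".
- **Recruitment.** Participants are asked to return the consent forms and questionnaires within seven days of receipt. Then: "The returned study documents will be checked for completeness, and the patient will then be entered into the randomisation database".
- **Group 1 (CBT manual + therapist support).** Treatment is one 60-minute session and "seven 30-min telephone/Skype sessions with a therapist over an eight-week period".
- **Initial estimates of efficacy outcomes.** The first outcome booklet is sent three months after randomisation.
- **Statistics and data analysis.** Treatment effects come from an intention-to-treat regression "adjusting for baseline values of the outcome, sociodemographic and clinical outcomes".

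**The concern.** The marker window is centred on questionnaire completion, and randomisation comes shortly afterwards. A value from the later half of the window is therefore likely to be a post-allocation measurement, possibly taken during CBT, yet it would be recorded as baseline. The article does not limit covariates to values dated before randomisation, and it does not prefer the earlier value when several fall in the window.

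Two things are at stake.

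- **The adjusted comparison.** Randomisation protects an adjusted estimate when the covariates were fixed before allocation. If a covariate is measured later and allocation has affected it, adjustment removes part of the effect being estimated. If allocation affects who is tested and when, the covariate also carries information on clinical course after allocation. Initial estimates of efficacy on fatigue and quality of life are a stated objective of the pilot.
- **The baseline table.** Entry requires no elevated inflammatory markers. A CRP or calprotectin value taken after allocation could appear in the table as if it described the patient at entry.

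The article also says that researchers are unblinded after randomisation and that there is no blinded data collector. Under the rule as written, someone who knows the allocation may choose between several eligible values.

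**Working it through.** The article gives no power calculation, effect size or SD, so there is no figure of its own to reproduce. Two checks apply: the timing, and the possible effect on the adjusted estimate.

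**1. Timing**

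Inputs from the article: a window of three months either side of the questionnaires, an eight-week CBT course, and randomisation after the returned documents are checked. Assumptions: three months = 13 weeks, so the window is 26 weeks; the lag L from questionnaire to randomisation is 0 to 4 weeks, because the article does not state it.

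- Share of the whole window after randomisation = (13 - L)/26.
- Share of the later half after randomisation = (13 - L)/13.

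| L (weeks) | Whole window | Later half |
|---|---|---|
| 0 | 13/26 = 50% | 100% |
| 1 | 12/26 = 46% | 92% |
| 2 | 11/26 = 42% | 85% |
| 4 | 9/26 = 35% | 69% |

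The window contains the whole CBT course only if CBT starts within 13 - 8 = 5 weeks of questionnaire completion. These are shares of calendar time. They equal shares of marker values only if test dates are spread evenly, which the article does not say.

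**2. Effect on the adjusted estimate (illustrative)**

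Every input here is an assumption. With T the arm (0/1) and e independent standard normal noise:

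- Pre-randomisation marker M0: standard normal.
- Baseline outcome: Y0 = 0.4 M0 + 0.9 e.
- Post-randomisation marker: M1 = 0.7 M0 + d T + 0.714 e.
- Outcome: Y = 0.5 Y0 + g M1 + (-0.5 - g d) T + 0.7 e, so the total effect of T is -0.50, roughly in SD units.
- Recorded marker: M1 with probability q, otherwise M0, independently of arm.
- Model: Y regressed on T, Y0 and the recorded marker, with 400,000 simulated patients.

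| q | d (SD) | g | M0 only | Recorded marker |
|---|---|---|---|---|
| 0.46 | 0 | 0.2 | -0.502 | -0.502 |
| 0.46 | 0 | 0.4 | -0.501 | -0.500 |
| 0.46 | -0.2 | 0.2 | -0.494 | -0.480 |
| 0.46 | -0.2 | 0.4 | -0.498 | -0.466 |
| 0.46 | -0.5 | 0.2 | -0.502 | -0.464 |
| 0.46 | -0.5 | 0.4 | -0.502 | -0.427 |
| 1.0 | -0.2 | 0.2 | -0.497 | -0.457 |
| 1.0 | -0.5 | 0.4 | -0.499 | -0.297 |

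With no arm effect on the marker (d = 0) there is no bias. With q = 0.46 and d between -0.2 and -0.5, the shift from -0.50 is 0.02 to 0.07, towards no effect. If every value were post-randomisation (q = 1.0), it would be 0.04 to 0.20. Using only M0 recovers about -0.50 throughout. The simulation does not model testing that differs by arm.

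**3. Scale**

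With 20 per arm, the unadjusted standard error of a standardised difference is about sqrt(2/20) = 0.32. The q = 0.46 shifts are 0.02/0.32 = 6% to 0.07/0.32 = 22% of that.

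**The case against.** The case on the other side has several parts.

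- **The covariates are not named.** The Statistics section lists no specific clinical covariate. Clinical could mean diagnosis, disease duration or number of surgeries, and the word baseline may govern the whole phrase. The final list is commonly left to an analysis plan. This stands: use of the markers as covariates is provided for, not established. It does not remove the point, because the section that sets the window gives adjustment as a purpose of these data.
- **The conflict may be one of wording.** The sentence in the Randomisation section may refer to the questionnaire booklet, with clinical data taken from the notes separately. That is possible, but the sentence covers all baseline information and the clinical data are described as collected at baseline. The two sections still need reconciling.
- **Most values may predate randomisation.** Patients are identified from their records at a clinic visit, and eligibility refers to inflammatory markers. Test dates may therefore cluster before or near recruitment. This stands: the true share is unknown and could be well below the calendar shares.
- **CBT may not move blood markers.** Nothing in the article says that it does, and patients with active disease are excluded, which leaves less room for an effect on CRP or calprotectin. This stands, and is why the likely size is small.

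A reader might infer more: that the adjusted effect is biased, that about half of the values will be post-randomisation, or that the window always spans the whole treatment course. The article supports none of these. Bias needs an effect of allocation on the marker or its testing, the half share needs evenly spread test dates and no lag, and full overlap needs CBT to start within about five weeks of the questionnaires.

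**Conclusion.** The concern holds as a conflict between two stated rules and a risk to the adjusted estimate. The article permits marker values that postdate randomisation to be treated as baseline, against its own statement on when baseline information is collected, and it provides for clinical data in the adjusted model. Bias is possible, not demonstrated. Its size cannot be derived from the article and is probably small for blood markers. The simulated shifts rest entirely on assumed values for the share of late values, the arm effect on the marker and the marker's relation to fatigue, so they show direction and order of magnitude only.

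The severity is moderate. The trial is a pilot that disclaims evidence of effectiveness, its feasibility outcomes are untouched, and the illustrative shifts at a 46% share are well inside the sampling error with 20 per arm. It is still worth correcting, because the estimates are meant to inform a definitive trial and the rule could be carried into it.

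**What to change.** Reconcile the Randomisation section with the Sociodemographic and clinical data section. State that, for the baseline table and for any covariate, the value used for each marker is the most recent one dated on or before randomisation. Record the test date with each value. Keep later values in separate fields for description only, and do not use them as covariates.

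This takes one sentence in the protocol and a date check at extraction. It also settles which value to take when several are available, so unblinded staff have no choice to make.

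The cost is some additional missing marker values, in a number the article does not allow to be estimated. A longer look-back would recover some of them, but older CRP or calprotectin values describe a relapsing disease less well, so that extension is optional.

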### Participant entry

Patient interviewees will be selected from those recruited for the RCT, who will have been evaluated prior to enrolment. The *Eligibility Screening Form* will be used to conduct pre-registration evaluation of participants for the RCT.

### Inclusion criteria

Patients who are currently experiencing fatigue (self-reported)Proof of diagnosis of IBD (record of diagnostic endoscopy in patient clinical notes); patients without this test will not be includedAged 18 years and overNo elevated inflammatory markers or other clinical features of active disease

### Exclusion criteria

Patients without a record of diagnostic endoscopy in their clinical notesElevated inflammatory markers or other clinical features of active diseaseCourse of CBT for any reason in the last yearCurrently enrolled in another trial involving a novel pharmacological interventionCurrent or planned pregnancy (pregnant women have been found to be significantly more affected by fatigue and sleep disturbances [131])Inability to give informed consent (for example, due to reduced mental capacity)Insufficient command of written and spoken English to understand study documents or procedures

### Statistics and data analysis

Due to the pilot design of the study a power calculation was not required. Data collected in the pilot study will be used to generate information for sample size calculations for a definitive full-scale effectiveness RCT. Based on similar pilot studies, a sample of 40 patients (20 per arm) was deemed large enough to provide useful information about the aspects that are being assessed for feasibility. It is recognised that the study may not be powered to detect meaningful differences in clinically important endpoints [91].

Patients will be recruited from an IBD outpatient clinic in London, UK, which is representative of the target study population of patients experiencing IBD-fatigue. The sample was based on the same inclusion/exclusion criteria that would be used in a future definitive full-scale effectiveness RCT. At the study site, a total of approximately 100–150 patients attend four IBD outpatient clinics each week. Assuming around 40% recruitment of eligible patients based on our earlier studies recruiting from this population [83], discussions with the clinical team and recruitment rates for intervention for fatigue in MS [57], our target aim of 40 patients should be reached within the six-month baseline data collection period. Taking into account an attrition rate based on prior research [132] of about 20% for each follow-up, we will aim to achieve a minimum sample size of 40 at baseline, in order to suitably assess outcomes at follow-up.

Primary and secondary measures at baseline along with recruitment rates, telephone session attendance, time spent on the intervention, Homework Sheet completion rates and withdrawal from intervention rates will be presented as means and standard deviations for approximately normally distributed continuous variables, medians and interquartile ranges for non-normally distributed variables, frequencies and percentages for categorical variables. Initial estimates of treatment effect on primary and secondary outcomes at the follow-up assessments will use an intention-to-treat (ITT) framework, implemented using a regression model, adjusting for baseline values of the outcome, sociodemographic and clinical outcomes. ITT analysis will compare the primary and secondary outcome measures at three months between the two randomised groups. ITT analysis will compare only primary outcome measures at six and 12 months between the two randomised groups. Where participants wish to withdraw from the intervention, we will attempt to retain them in the data collection, unless they express a wish to be withdrawn completely.

As this is a pilot study, it is not intended that the study is powered to detect significant differences on the primary or secondary outcome measures. Qualitative data will also be recorded. Protocol conforms to Standard Protocol Items: Recommendations for Interventional Trials (SPIRIT). See Additional files 1 and 2 at the end of the manuscript for SPIRIT Figure and Checklist.

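### The effect model sets no limit on its sociodemographic and clinical covariates: entering the 21 listed would be too many for 40 patients or fewer, and eight of them may be measured after randomisation

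*Protocol article*

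**What the plan says.** The Statistics and data analysis section of the protocol article gives the effect model as an intention-to-treat comparison "implemented using a regression model, adjusting for baseline values of the outcome, sociodemographic and clinical outcomes". Primary and secondary outcomes are compared at three months, and the primary outcome alone at six and 12 months. No covariate is named beyond the baseline outcome and the two categories, and there is no limit or selection rule.

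The Sociodemographic and clinical data section says what those categories contain and gives several purposes for collecting the data, among them to "make the results of the RCT more clinically relevant and appropriately adjusting statistical data analysis". The first list reads "Sociodemographic data collected will include: age; gender; marital status; education status; employment status; and living arrangements". The clinical list begins with diagnosis, co-morbidities, faecal calprotectin and medications, and ends with seven blood markers. The same section says that no extra blood tests will be done when recent results are missing from the records. It accepts one value per marker if that value falls within three months before or after completion of the baseline questionnaires.

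On numbers, the Statistics section says "a sample of 40 patients (20 per arm) was deemed large enough to provide useful information" and allows for "an attrition rate based on prior research [132] of about 20% for each follow-up".

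**The concern.** Read together, the two sections commit the analysis to two whole categories of covariates, and one section itemises them. A trial of 40 patients cannot support 21 covariates. Each uninformative one costs a residual df and widens the interval for the arm effect.

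The Methods and design section makes initial estimates of efficacy and the sample size of the definitive trial explicit objectives. An effect estimate on very few df is a poor starting point for either. If the covariate set is cut down only after the data are seen, the estimate is open to selective choice.

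A second problem does not depend on how many covariates enter. A laboratory value taken after randomisation may already reflect treatment, and adjusting for it can bias the comparison that randomisation protects.

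**Working it through.** **The plan's own figure.** The 40 rests on similar pilot studies. The Statistics section states: "Due to the pilot design of the study a power calculation was not required". There is no formula to reproduce, so only the expected follow-up numbers can be derived.

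**Parameter count** (lists in Sociodemographic and clinical data):
- Sociodemographic: age, gender, marital status, education, employment, living arrangements = 6.
- Clinical: diagnosis, co-morbidities, calprotectin, medications, time since diagnosis, surgeries, smoking, exercise = 8; haemoglobin, ferritin, albumin, CRP, platelets, B12, folate = 7; total 15.
- 6 + 15 = 21 covariates. Adding intercept, arm and baseline outcome gives 24 parameters at one term each.
- This is a minimum. Smoking has three stated levels, which makes 25. If marital, education, employment and living status also took two terms each (an assumption), there would be 29.

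**Residual df = n − parameters**, under each reading of the attrition figure. Compounding gives 40 × 0.8 = 32, 40 × 0.8² = 25.6 and 40 × 0.8³ = 20.5.

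| Reading | n at 3 / 6 / 12 months | df, 24 parameters | df, 25 parameters |
|---|---|---|---|
| 20% lost at each successive visit, observed outcomes only | 32 / 26 / 20 | 8 / 2 / −4 | 7 / 1 / −5 |
| 8 patients lost per visit, observed only | 32 / 24 / 16 | 8 / 0 / −8 | 7 / −1 / −9 |
| 20% of baseline missing at every visit | 32 / 32 / 32 | 8 / 8 / 8 | 7 / 7 / 7 |
| All 40 kept by imputation | 40 / 40 / 40 | 16 / 16 / 16 | 15 / 15 / 15 |

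A negative entry means the model has more parameters than patients and cannot be fitted.

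**Cost in precision.** A simulation with 21 independent covariates of no prognostic value compared the full model with one containing arm and baseline outcome only. The interval-width ratio is the median standard-error ratio multiplied by the ratio of the t critical values:
- n = 40: 1.50 × (t on 16 df ÷ t on 37 df) = 1.50 × (2.120 ÷ 2.026) = 1.57.
- n = 32: 1.84 × (t on 8 df ÷ t on 29 df) = 1.84 × (2.306 ÷ 2.045) = 2.07.
- n = 26 gives about 6 and n = 25 about 24, so the six-month figure turns on how 25.6 is rounded and should not be relied on.

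If some covariates are prognostic, the widening is smaller.

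**Laboratory covariates.** Calprotectin plus the seven blood markers makes eight. The article gives no availability rate. If each value were on file for 90% of patients (assumption), complete records would range from 0.9⁸ = 43% when gaps are independent to 90% when the same patients lack everything. At 80% availability the range is 0.8⁸ = 17% to 80%.

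**Timing.** Under Recruitment, patients are randomised after the completed baseline questionnaires are returned, within seven days of receipt. Under Group 1, therapy runs for eight weeks. A marker accepted up to three months after the questionnaires can therefore be measured before randomisation, during therapy or after it ends.

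**The case against.** The strongest reply is that the article names two categories and never says that every listed variable enters. The data have other stated purposes: describing the sample and making the results clinically relevant. Items such as medication name, dose and frequency look descriptive. A condensed article may leave the choice of covariates to an analysis plan that is not shown. That stands, and it makes the df figures conditional. It does not remove the point, because the article does state an adjustment set, and followed as written that set is too large.

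A reader might infer that the model is nearly saturated at six months and impossible at 12. The document does not support this as a flat statement. It needs full entry of both lists, attrition that accumulates across visits, and analysis of observed outcomes only. If 20% are missing at every visit, or if all 40 are kept by imputation, the 24-parameter model can be fitted throughout.

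A reader might also infer that most patients would drop out for want of a laboratory value, emptying the intention-to-treat label. That rests on assumed availability, on independence between tests often ordered together, and on complete-case handling that the article does not state. The article also says these data are routine in standard care, and eligibility requires no elevated inflammatory markers.

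The phrase clinical *outcomes* may be loose wording, since the data are described as collected at baseline. The worry about timing does not need that phrase; it rests on the stated window for marker values.

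Finally, the pilot disclaims power and any evidence of effectiveness, and does not say that this model's residual SD will feed the later sample size. Both are true and limit the consequence, but initial efficacy estimates remain a stated objective.

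**Conclusion.** The point holds in conditional form. If the two listed sets are entered in full, the model has at least 24 parameters, with 16 residual df at n = 40 and 8 at n = 32. With uninformative covariates the interval for the arm effect is then about 1.6 to 2.1 times as wide as it need be. Only if attrition also compounds and observed outcomes alone are analysed do about 2 df remain at six months (n about 26) and none at 12 (n about 20). Full entry is too much on every reading of the attrition figure, even with all 40 patients kept.

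The timing problem stands independently of these assumptions: the marker window allows adjustment for values measured after randomisation. How many patients would lack a laboratory value cannot be determined from the article.

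**What to change.** In Statistics and data analysis, replace the adjustment clause with wording such as: the effect model contains arm, the baseline value of the same outcome and at most one or two named covariates fixed in advance and measured before randomisation (for example, diagnosis, CD or UC); no variable measured after randomisation is included; all other sociodemographic and clinical data are descriptive.

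With diagnosis as the only extra covariate there are 4 parameters, leaving 36 df at n = 40, 28 at n = 32 and 16 at n = 20, so the model can be fitted on every attrition reading above. Diagnosis is an example; the sponsor may justify another choice. In Sociodemographic and clinical data, the marker window can stay for description, provided that those values do not enter the model.

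The change is wording only and needs no extra data. Its small cost is that a possibly prognostic variable goes unadjusted.
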